### Objectives {7}

The overall objective of this study is to test the therapeutic effects and mechanisms of action of (i) a single dose of ketamine, (ii) a reward imagery rt-fMRI NFT, and (iii) the combination of those interventions compared to placebo conditions in individuals with CUD.

Therapeutic effects of the interventions—alone and combined—are measured via the investigation of changes in cocaine use assessed by questionnaires.

Mechanistic effects of the interventions—alone and combined—are measured via the investigation of (a) ketamine-induced changes in accumbal glutamate levels with ^1^H-MRS.

and (b) effects of the reward imagery rt-fMRI NFT on reward processing.

### Trial design {8}

The trial adopts a randomised, placebo-controlled, double-blind, parallel-group, single-centre design with a superiority framework. The treatment combination among the four arms, each consisting of 30 participants, is depicted in Fig. 1.

**Fig. 1 Fig1:**
[figure not shown]
Study flow chart. Illustrating timeline and group assignments for participants in the clinical trial

## Methods: participants, interventions and outcomes

Study methods have been reported in accordance with the Standard Protocol Items: Recommendations for Interventional Trials (SPIRIT) reporting guidelines [45] (see Additional file 1).

### Study setting {9}

The first four visits take place on-site at the Psychiatric University Clinic Zurich in Switzerland, followed by a fifth visit conducted remotely via video call, and the final visit involves completing an online survey.

### Eligibility criteria {10}

#### Inclusion criteria

Informed consent as documented by signatureMale and female cocaine users 18 to 55 years of ageDSM-5 diagnosis of CUDWillingness to comply with the study protocol as explained by the investigatorNormal level of language comprehension (German or Swiss-German)

#### Exclusion criteria

Current or lifetime psychotic disordersHistory of severe substance-induced psychosisCurrent or lifetime bipolar I or II disordersCurrent suicidalityPrevious suicide attempts during the last 2 yearsCurrent severe alcohol use disorderCurrent severe cannabis use disorderCurrent moderate or severe stimulant use disorder (other than cocaine)Current moderate or severe benzodiazepine use disorderCurrent opioid use disorderFirst-degree relatives with psychotic disordersBeck Depression Inventory Score greater than 25Unmedicated or unstable hypertensionSevere illness (e.g. myocardial ischemia or arrythmias, severe pulmonary secretions, glaucoma, congestive heart failure or angina, significant renal or hepatic impairment)Acute infection (e.g. pulmonary or upper respiratory tract infection)Insufficient treated or uncorrected hyperthyroidismSevere CNS-related traumas or disorders (e.g. stroke, cerebral trauma with loss of consciousness over more than 24 h, epilepsy)Increased intracranial pressureMedication directly affecting glutamate signalling (e.g. anticonvulsant medication)Any unstable psychoactive medication (no changes in compounds within the last 4 weeks before the start of study)Pregnancy or lactationWomen of childbearing potential with no use of medically accepted contraceptives (e.g. condoms, contraceptive diaphragm, birth control pill, hormone injection, intrauterine device)BMI > 35Allergy, hypersensitivity, or other adverse reaction to previous use of ketamineContradictions to magnetic resonance imagingConcurrent participation in other clinical study

### Who will take informed consent? {26a}

Participants receive the study information and informed consent at least 24 h before the first visit (t0). Delegated investigators obtain written informed consent from all eligible participants on the first study visit (t0) before conducting any trial-related procedures and before collecting any data. Furthermore, participants will receive a copy of the signed consent form.

### Additional consent provisions for collection and use of participant data and biological specimens {26b}

There is a separate consent form for the further assessment of biomarkers in blood plasma samples and optional secondary use of data.

## Interventions

### Explanation for the choice of comparators {6b}

Two forms of interventions are combined and compared: a single dose of ketamine and a reward imagery rt-fMRI NFT. Both interventions are placebo-controlled, which leads to four study arms with the following intervention combinations: (i) rt-fMRI NFT/placebo, (ii) rt-fMRI NFT/ketamine, (iii) sham NFT/placebo, and (iv) sham NFT/ketamine. This study group allocation allows for comparing each active treatment to its placebo treatment and, in addition, the combination of both interventions to a placebo study arm, that is, study arm (iii) sham NFT/placebo.

### Intervention description {11a}

#### Ketamine

On the screening visit (t0), all participants are prepared for the ketamine/placebo infusion by clarifying questions and providing information, and thereby, creating a safe framework for the subsequent intervention at intervention visit I (t1). During this preparation, participants are encouraged to develop a guiding motto that can help if challenging experiences arise during the ketamine/placebo infusion (e.g. breathe deeply, be curious, observe without judgment, surrender). Ultimately, the modifications they intend to implement with regards to their cocaine consumption over the course of the study period (i.e. specific goals for the reduction of cocaine use) are established together. For safety reasons, all participants are instructed to abstain from using illegal substances for 3 days and from alcohol for 2 days before intervention visit I (t1).

If the participant has been found eligible for study participation, the participant is allocated to one of the four study arms: (i) rt-fMRI NFT/placebo, (ii) rt-fMRI NFT/ketamine, (iii) sham NFT/placebo, and (iv) sham NFT/ketamine. The hospital pharmacy receives an automatic email generated by the data management system with information about the study arm allocation and prepares accordingly either an infusion bag of 1 mg/ml ketamine hydrochloride (Ketalar®) in 0.9% saline or a 0.9% saline solution as placebo. Both solutions have a total volume of 120 ml to ensure a standardised administration via the infusion pump (Space® Infusion Pump). The dose of ketamine is administered based on body weight at a rate of 0.71 mg/kg, given intravenously over 40 min. The dosage and route of administration of ketamine correspond to those used in previous studies investigating ketamine’s efficacy in CUD [26, 46]. Doses are generally higher in studies with SUD than in studies with depression, based on findings that individuals with alcohol use disorder may show cross-tolerance to ketamine [47]. The dose of 0.71 mg/kg or higher has consistently shown to have a good tolerability in populations with SUD [26, 46, 48–52].

On intervention visit I (t1), when the ketamine/placebo infusion is administered, at first, baseline magnetic resonance (MR) measures are performed as a reference for the ketamine-induced changes, followed by identical MR measures that are performed during the ketamine/placebo infusion to capture glutamate levels over the course of the 40-min infusion. The MR measures include a ^1^H-MRS sequence (40 min) and during all MR measurements, participants are listening to an instrumental music playlist. Following the baseline MR measurements, participants take a short break outside of the MR scanner before they perform the first session of reward imagery rt-fMRI NFT (see intervention description—reward imagery rt-fMRI NFT). After the rt-fMRI NFT, participants have another short break outside of the MR scanner and have a peripheral vein cannula placed on their forearm. Before the start of the ketamine/placebo infusion, participants perform a 10-min audio-guided mindfulness-based exercise (body scan) to shift their focus inwards. Then, the infusion is started simultaneously with the ^1^H-MRS measurement. After 10 min of steady-rate infusion, a bolus at half of the total dose is administered for the next 10 min. The infusion then returns to a steady-rate for the remaining 20 min. After the infusion, participants perform the second reward imagery rt-fMRI NFT right afterwards. The whole procedure for intervention visit I (t1) is depicted in Fig. 2.

**Fig. 2 Fig2:**
[figure not shown]
Timeline for intervention visit I (t1). Participants perform two ^1^H-MRS measurements (baseline and during the ketamine/placebo infusion), and two reward imagery rt-fMRI NFT sessions (before and after the ketamine/placebo infusion). Blood withdrawal takes place pre and post infusion. Time points for questionnaires are indicated with grey arrows

Throughout the whole day, participants are asked about their cocaine craving and affective state on visual analogue scales. In addition, following the infusion, they answer questions about subjective effects during the administration, and a qualitative interview is conducted at the end of intervention visit I (t1) to capture the personal experiences during the ketamine/placebo infusion. Medical coverage is provided until 3 h post-infusion, and participants are discharged only after they have been screened for suicidality. Besides blood pressure monitoring pre- and post-infusion, the following safety measures are taken on intervention visit I (t1): a drug urine quick test, an alcohol breath test, and individuals of childbearing potential must take a urine pregnancy quick test.

For further serum analysis of the neuroplasticity marker BDNF, blood is withdrawn 30 min prior and 2 h post infusion.

During the intervention visit II (t2), which will be held 7 to 14 days after the intervention visit I (t1) an ^1^H-MRS measurement to assess accumbal glutamate levels will be conducted during a craving paradigm, namely a video of 22.5 min that reliably induces craving in cocaine users [19].

#### Reward imagery rt-fMRI NFT

As with ketamine, as soon as the participant is randomised, an automatic email is sent by the data management system to the study team with the blinded rt-fMRI NFT code (i.e. group “dog” or group “cat”). In total, each participant takes part in three reward imagery rt-fMRI NFT sessions within the study. The first two sessions take place at intervention visit I (t1). One before and one after the ketamine/placebo infusion, and the third training session takes place at intervention visit II (t2).

As preparatory training, participants are asked to do the Prospective Imagery Task [53] during the screening visit (t0), where they need to imagine rewarding situations.

As a first step at the intervention visit I (t1), participants receive a standardised oral instruction about the following reward imagery rt-fMRI NFT task. The instruction is identical for the sham and for the real rt-fMRI NFT. The experimenter explains that one is capable of increasing neural activity in brain regions important for reward processing by using positive imagery. This positive imagination can contain any rewarding situation (e.g. sexual experience, anticipation of food, …). The only two rules are that the reward imagery must not be substance-related, and participants are not allowed to use strategies that involve music, such as playing an instrument or listening to music, due to possible activation of the Heschl’s gyrus, which is the chosen sham brain region. The reward imagery rt-fMRI NFT paradigm takes around 25 min. The paradigm for training one and three comprises five runs: a practice run without feedback, followed by three training runs with feedback, and at last a transfer run without feedback. Training session two comprises only three practice runs with feedback. Within each run, there are four blocks where participants are alternately instructed to either upregulate their activity in the target region by using a strategy of positive imagination or by counting backward to keep the activity in the target region at rest. The activity of the target region is visualised to the participant in the form of a bar with a ball that moves upwards when positively activated or stays at the bottom when unchanged, respectively, to provide feedback about the current performance in regulating one’s own activity. The feedback presentation is in an intermittent fashion right after each block (i.e. “positive imagination” and “counting backward”) (illustrated in Fig. 3). We have chosen intermittent feedback, due to reduced cognitive demands and confounding effects on reward-related activity [54].

**Fig. 3 Fig3:**
[figure not shown]
Task design (adapted from [41] and [84]). During training session one and three, each participant undergoes five runs, each one composed of “Count” (20 s) followed by “Imagination” (20 s), then repeated four times. The first and last runs (practice and transfer run) only showed instructions with no visual feedback. During the three training runs, we instruct participants to use rewarding non-drug imagery to raise the ball during “Imagination” and counting backwards to keep the ball down during “Count”

At the beginning of each training session, either the VTA mask (probabilistic mask as defined by [55]) or the mask of the Heschl’s gyrus, the sham region (AAL Atlas) is co-registered with the functional MR images to minimise displacement artifacts due to head movements. Despite the displayed feedback, which is provided from different brain regions, all procedures and instructions are identical for the participants who receive sham NFT as for those who receive the real rt-fMRI NFT. The intervention is double-blinded.

The feedback signal is calculated with OpenNFT [56], a software package for rt-fMRI NFT. The feedback signal is estimated based on activity levels in the respective target region (i.e. VTA or Heschl’s gyrus) as the area under the curve (AUC) between rest and regulation. The feedback is calculated as follows: double of the forehand-related rest block compared to the regulation block (i.e. “positive imagination” and “counting backward”).

Between each run, participants answer a short in-between questionnaire that includes subjective questions about their feelings and motivation during the last run, the applied strategies, the contingency between received feedback and used strategy, and whether they were looking at the cross during the rest block (see Additional file 2, Table 1).

For the control condition, sham NFT, an alternative brain region was chosen. The signal for the feedback is extracted from the Heschl’s gyrus mask (AAL Atlas).

When the reward imagery rt-fMRI NFT paradigm is complete, participants answer a debriefing questionnaire outside of the MR scanner that includes subjective questions about how they liked it, how good their skills were in general, the strategies used, whether they used substance-related or music-related strategies, and whether they felt an improvement (see Additional file 2, Table 2).

The second training session takes place right after the finished ketamine/placebo infusion during the intervention visit I (t1). During this training session, the participant does not need to answer the questions in between. The procedure of the third training session during intervention visit II (t2) is the same as for the training session one.

### Criteria for discontinuing or modifying allocated interventions {11b}

Each participant is informed that the participation in the study is voluntary and that he/she may withdraw from the study at any time. The study may also be discontinued by the investigator if the participant does not comply with the study protocol, if further study participation would bear a risk to the health of the participant, or in case of pregnancy.

No modifications to the allocated treatment will be made.

### Strategies to improve adherence to interventions {11c}

Both interventions, ketamine and reward imagery rt-fMRI NFT, are carried out on site. Therefore, the investigator monitors the adherence to both interventions directly. The ketamine/placebo infusion is administered to the participant by medically trained staff at the intervention visit I (t1). Reward imagery rt-fMRI NFT is closely guided by the investigators. The compliance to the application for ecological momentary assessment (EMA) is continuously monitored. In case of an insufficient response rate in the EMA, the participant will be contacted by an investigator. Additionally, a motivational monetary bonus is given if the participant answered at least 80% of the EMA requests. Adherence to the study protocol is continuously monitored by recording concomitant medication, urine pregnancy testing, and drug screening with urine analysis and questionnaires.

### Relevant concomitant care permitted or prohibited during the trial {11d}

#### Concomitant therapy

Psychotherapeutic or psychological treatment from third parties needs to be suspended between intervention visit I (t1) and intervention visit II (t2), which is a minimum of 7 and a maximum of 14 days. Moreover, participants are instructed to inform the study personnel about therapies or operations that take place during the first four visits of the study.

#### Prohibited medications

Medications directly affecting glutamate signalling, e.g. anticonvulsant drugs as well as ketamine use during the study are not desirable and are monitored throughout the study. In addition, all new regular uses or dose changes of already existing concomitant medication are also monitored throughout the study.

### Provisions for post-trial care {30}

All participants are advised to contact the study team at any point during the study period if there are questions or concerns about the intervention or the study. Given the absence of anticipated harm due to study participation, no specific provision for post-trial or ancillary care is foreseen by the study protocol. However, any damage developed in relation to study participation is covered by the insurance.

### Outcomes {12}

All outcomes are summarised in Table 3 (see Additional file 2, Table 3) and their timepoints are outlined in Table 1.

**Table 1 Tab1:** Participant timeline

Study period						
	Screening visit	Intervention visit I	Intervention visit II	Follow-up visit	Virtual visit	Follow-up survey
Visit	t0	t1	t2	t3	t4	t5
Time	− 84 days to − 10 days	0	+ 7 days to + 14 days	+ 35 days to + 49 days	+ 56 days (± 7 days)	+ 168 days (± 14 days)
Patient information and informed consent	x					
In-/exclusion criteria	x					
Demographics	x					
Body weight	x					
Electrocardiogram	x					
Mini-International Neuropsychiatric Interview, DSM-IV	x					
Routine laboratory tests	x					
Randomisation	x					
Pulse and blood pressure	x	x				
Urine pregnancy test (women only)		x	x			
Laboratory test for neuroplasticity marker	x	x				
Drug urine quick test		x				
Drug urine laboratory analysis	x	x	x	x		
Concomitant medication form	x	x	x	x		
Interview for psychotropic drug consumption	x	x	x	x	x	
Timeline follow back, version for cocaine use	x	x	x	x	x	x
Visual analogue scale for change	x	x	x	x	x	x
Obsessive compulsive cocaine use scale	x		x	x	x	x
Beck Depression Inventory	x		x	x		
Domains Of Pleasure Scale	x		x	x	x	x
Trait Hedonic Capacity Scale	x		x	x	x	x
Rosenberg Self-esteem Scale	x		x	x		x
Questionnaire for Self-Efficacy, Optimism, and Pessimism	x		x	x		x
Stress Questionnaire, Subscale of Stress & Coping Inventory	x			x		x
Generalised expectancies for Negative Mood Regulation	x			x		
Prospective Imagery Task	x					
Study Medication Administration		x				
Hood’s Mysticism Scale		x				
Five-Dimension Altered States of Consciousness Questionnaire		x				
Neurofeedback in between Questionnaire		x	x			
Neurofeedback Post Questionnaire		x	x			
MRI Safety Form		x	x			
Magnetic Resonance Spectroscopy		x	x			
Real Time Functional Magnetic Resonance Neurofeedback Training		x	x			
Visual analogue scale for affective state		x	x			
Visual analogue scale for cocaine craving		x	x			
Qualitative interview		x	x	x		
Serious adverse events		x	x	x	x	

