
#### Other outcomes of interest

An electrocardiogram (ECG) and a clinical interview will be conducted and evaluated at the screening visit (t0) to ensure mental and physical health. To capture the consumption pattern of cocaine and potentially other psychoactive substances, the Interview for Psychotropic Drug Consumption [72] will be conducted on screening visit (t0), intervention visit I (t1), intervention visit II (t2), follow-up visit (t3), and virtual visit (t4).

On intervention visits I (t1) and II (t2) and the follow-up visit (t3), we are conducting qualitative interviews to assess acute and sustained effects of the interventions on the subjective experience and the predictive value of those effects [73, 74].

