### Participant timeline {13}

The schedule for data collection and visits is shown in Table 1. After initial establishment of contact, interested candidates are invited for a screening visit (t0), where the eligibility criteria are checked, and suitable participants are randomly assigned to one of the four study arms. The assigned treatment intervention is performed at intervention visit I (t1) and II (t2). The follow-up visit (t3) assesses first effects of the intervention on behavioural measures. Between each of the first five visits, participants are asked to use an EMA application [71] on their smartphones. To measure long-term effects, there is a virtual visit (t4) and a follow-up survey (t5) scheduled.

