### Adverse event reporting and harms {22}

All observed or volunteered abnormal safety endpoints are recorded in the data management system. The investigator promptly reviews documented adverse events (AE) or other abnormal safety endpoints to determine if (i) the abnormal safety endpoint should be classified as an AE, (ii) if there is a reasonable possibility that the AE was caused by the investigational drug, and (iii) if the AE meets the criteria for a serious AE (SAE). The investigator is responsible for SAE reporting to the sponsor-investigator, who will conduct a documented evaluation. Additionally, all SAE must be reported to the local Ethics Committees of Zurich and Swissmedic by the sponsor-investigator.

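### The visit schedule lists only serious adverse events, while the harms section means to record all events but states only passive capture, so non-serious harms are likely to be under-recorded

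*Protocol article*

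**What the plan says.** The Participant timeline section {13} presents the table as the schedule: "The schedule for data collection and visits is shown in Table 1". In Table 1, under Outcomes {12}, the only row for events is "Serious adverse events". It is marked at t1, t2, t3 and t4, and is blank at t0 and t5. There is no row for adverse events in general.

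Adverse event reporting and harms {22} is broader: "All observed or volunteered abnormal safety endpoints are recorded in the data management system". The investigator then decides whether the finding is an adverse event, whether the drug may have caused it, and whether it is serious. Seriousness is therefore settled after recording and is not a condition for it.

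On the infusion day, Intervention description {11a} states: "Medical coverage is provided until 3 h post-infusion, and participants are discharged only after they have been screened for suicidality". Safety outcomes adds that current suicidality is asked about at every on-site visit, which includes t2 and t3.

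Other contacts could bring events to light:
- At t1, t2 and t3, "we are conducting qualitative interviews to assess acute and sustained effects of the interventions on the subjective experience" (Other outcomes of interest).
- The neurofeedback debriefing at t1 and t2 "includes subjective questions about how they liked it, how good their skills were in general".
- On medication, "all new regular uses or dose changes of already existing concomitant medication are also monitored throughout the study" (Prohibited medications). The form is marked at t0 to t3.
- The Beck Depression Inventory is given at t0, t2 and t3.
- Ecological momentary assessment runs between visits up to t4. Its listed content is cocaine use, craving, affect and reward sensitivity.

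**The concern.** The schedule and the harms section differ in scope. Staff who work from Table 1 would look for serious events only. Staff who work from {22} would record everything, but only what they happen to notice or what a participant chooses to mention. Neither place tells them to ask.

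Ketamine, alone and with neurofeedback, is studied here as a possible treatment. Its non-serious effects therefore matter to participants and to later users. Events that depend on being noticed or mentioned tend to be under-counted, and bodily complaints that begin after the participant has gone home are the most exposed. The efficacy and mechanistic analyses are not touched.

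**Working it through.** The plan gives no figure to reproduce. The check compares the schedule with the text, followed by simple arithmetic on the visit windows.

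**1. Scope.** Table 1 marks serious events at 4 of 6 time points and adverse events in general at 0 of 6. Section {22} covers any seriousness. The two differ in scope without contradicting each other, since {22} does not limit recording to serious events and sets no end date for it.

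**2. Mode of capture.** Section {22} names two routes, observation and volunteering. The section on post-trial care {30} adds that participants may contact the team with concerns, and Concomitant therapy {11d} asks them to report therapies and operations during the first four visits. These also rely on the participant to come forward. No section describes a general question put to every participant.

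**3. What the other contacts ask about.**

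| Contact | When (t1 onwards) | Subject |
|---|---|---|
| Suicidality screen | on-site visits | suicidality (a solicited safety check) |
| Beck Depression Inventory | t2, t3 | depressive symptoms |
| Qualitative interview | t1, t2, t3 | subjective experience |
| Neurofeedback questionnaires | t1, t2 | training experience |
| Medication form | t1, t2, t3 | concomitant medication |
| Ecological momentary assessment | between visits to t4 | cocaine use, craving, affect, reward sensitivity |

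Only the first is listed as a safety outcome. None is described as covering bodily complaints systematically.

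**4. The t4 video call.** Table 1 marks seven rows at t4: psychotropic drug interview, timeline follow back, scale for change, craving scale, two pleasure scales, and serious adverse events. Six concern substance use, motivation, craving or pleasure. One is an event row. The on-site suicidality screen, the Beck Depression Inventory, the interview and the medication form are not marked or required there.

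**5. Length of the intervals (Table 1 windows).**
- t1 to t2: 7 to 14 days.
- t2 to t3: 35 − 14 = 21 days to 49 − 7 = 42 days.
- t3 to t4: 49 − 49 = 0 days to 63 − 35 = 28 days.
- t1 to t4: 56 ± 7, so 49 to 63 days.

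**6. Illustration only; the capture rate s is assumed.** Ketamine participants: 2 arms × 30 = 60. If no case of an event is recorded, the 95% upper bound on its true rate is (1 − 0.05^(1/60)) / s.
- s = 1: 1 − 0.05^(1/60) = 4.87%.
- s = 0.9: 4.87% / 0.9 = 5.4%.
- s = 0.7: 4.87% / 0.7 = 7.0%.
- s = 0.5: 4.87% / 0.5 = 9.7%.

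This shows how incomplete capture weakens a statement that an event was not seen. It does not measure the shortfall in this trial, because the document gives no value for s.

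**The case against.** The strongest objection is that this is a condensed article. Protocol version 2.4 exists and is not shown, and how events are elicited at visits is ordinary detail for the full protocol or the case report form. Nor is Table 1 a reliable basis for arguing from silence. It has no row for ecological momentary assessment or for the suicidality screen. It marks the urine quick test at t1 only, although Safety outcomes requires it at both intervention visits. It places the negative mood regulation scale at t3, where Secondary outcomes says t4.

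Much of this stands, and it limits the point. A reader might infer that no enquiry of any kind about non-serious events is scheduled once the 3 h coverage ends. The documents do not support that. The suicidality screen at t2 and t3 is a solicited safety check that can detect a non-serious event, the Beck Depression Inventory is given at the same visits, and medication changes are monitored through the study. The 3 h figure is the duration of medical coverage and is not described as the end of adverse-event enquiry. A reader might also infer that only serious events are to be recorded, and {22} says otherwise.

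What the objection does not remove is what the article states. It writes a serious-only row in the schedule and names only passive capture in {22}. If the full protocol has a standard question, both statements describe it incompletely. If it has none, the gap is real. A correction is due in either case.

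**Conclusion.** The point holds as a minor one. The schedule and the harms section differ in scope, the stated capture is passive, and the article describes no general enquiry about non-serious events, least of all at t4. Non-serious harms, mainly bodily complaints after discharge, are likely to be under-recorded over the 49 to 63 days between infusion and t4. The size of the shortfall cannot be derived from the document.

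The conclusion assumes that the article's text reflects practice and that spontaneous reports miss some events that a direct question would find. The consequence is confined to harms reporting.

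**What to change.** Relabel the Table 1 row *Adverse events (serious and non-serious)* at the same visits, t1 to t4. At each of these visits, ask every participant in all four arms one standard, non-leading open question, for example: *Have you had any health problems since the last visit?* At t1 the reference point would be the start of the infusion or training. Amend {22} to read *observed, volunteered or elicited by standard questioning*, and note the date of the change. If the full protocol already contains such a question, only the row label and the {22} wording need correcting.

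The cost is one row label, one sentence and one question at existing contacts, including the t4 video call. There will be more minor events to record. Participants who passed some visits before the change will have been asked differently, so harms tables should show the change date. The Trial status section reports three completers at submission and recruitment until about spring 2026, so an early change would cover many participants.
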